#### Integrated analysis

2.6.1.

Data from the PA endpoints (PA, muscular fitness, and CRF describing variables) collected for each individual will be mapped in a principal component analysis plot. Hierarchical cluster analysis will be applied to the PCA scores in order to extract 3 clusters corresponding to low, medium, and high PA scores. The significant differences between the group of individuals will be challenged in a supervised partial-least square discriminant analysis (cross-validation ANOVA and permutation test). All the collected biological data, whether clinical or omics, will be examined in each of the 3 groups of individuals defined therefrom (low, medium, and high PA outcomes). Variables selection to fit the class assignment will be performed independently for each kind of variable with a sight of sparsity. PLS-discriminant analysis (orthogonalized or not), sparse-PLS, and machine-learning methods such as random forest will be applied and resilient variables, selected with all the methods, retained. Statistical models will be built on 4/5 of the population, and their performance assessed by predicting the 1/5 unknowns. This will be iterated 10 times. Complementary AUROC analyses will confirm biomarkers selection robustness. The most resilient variables (expected ∼20 variables from any origin) will be saved, and computed in a final PLS-discriminant analysis. From there, an equation calculated from the beta score of the PLS algorithm and the variable values will be established (using the NIPALS algorithm) to give each individual a score value (with 95% confidence intervals) that fits its PA class (e.g., low, medium, high). This equation will be challenged in the subgroup of the core cohort after the educational intervention. Also, the predictive robustness of the individual score value will be challenged to identified confounding factors (BMI, age, pubertal state, and gender, diet and lifestyle-related factors including sleep behaviour) in a logistic regression model.

After biomarkers discovery, the same methodology as above will be used to identify the biological variables that are related to each PA group, but with much less sparsity. This will allow to examine the molecular regulations that occur at the pathway level. Multi-block PLS method will determine the most influencing kind of variables (miR, transcriptomics, lipidomics, metabolomics, clinics) on group assignment. Pathway enrichment analyses will be also used to provide a biological explanation output. Some focus on specific pathways using in silico reconstituted pathway gathering several omics levels could be also performed (ingenuity pathway analysis, MetExplore, and/or Metscape plugin of cytoscape).

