#### Participants

2.3.1.

A total of 180 volunteers (core cohort) will be recruited and distributed into two age groups: prepubertal individuals (*n* = 90), including children, from 8 to 10 years, and postpubertal adolescents (*n* = 90) from 13 to 15 years. Each group will include three subgroups (*n* = 30) of subjects with normal weight (NW), overweight (OW), and obesity (OB) as defined by WHO criteria (38). Volunteers will be equally distributed between both sexes in each group and subgroup. The sample size of the core cohort is based on our previous expertise in different projects aimed at identifying biomarkers (mainly gene expression biomarkers analysed in blood cells by omics techniques), in which we used even a lower number of volunteers [e.g., studies (24, 39)]. Moreover, the combination/integration of different types of biomarkers that will be performed (based not only on gene expression, but also considering lipidomic, metabolic and miRNA profiles) makes its more likely to be able to detect significant metabolic differences and more robust biomarkers. Additionally, the number of volunteers of the core cohort is also expected to be sufficient to achieve the required sample size for the intervention study, which was calculated as explained in Section 2.4.

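### The PA classes are clustered over both age groups with no age or sex scaling stated, and markers are selected before age and sex are examined, so age markers may be selected as PA markers

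*Protocol article*

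**What the plan says.** Section 2.3.1 recruits two separate age bands in equal numbers: "prepubertal individuals (*n* = 90), including children, from 8 to 10 years, and postpubertal adolescents (*n* = 90) from 13 to 15 years". Each band has 30 participants with normal weight, 30 with overweight and 30 with obesity, and the sexes are balanced throughout.

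Section 2.6.1 then sets a fixed order of steps:

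1. "Data from the PA endpoints (PA, muscular fitness, and CRF describing variables) collected for each individual will be mapped in a principal component analysis plot".
2. "Hierarchical cluster analysis will be applied to the PCA scores in order to extract 3 clusters corresponding to low, medium, and high PA scores".
3. "The significant differences between the group of individuals will be challenged in a supervised partial-least square discriminant analysis", with a permutation test. The predictors are not named. Clinical and omics data first appear in the next sentence.
4. Biological variables are selected for their fit to the classes, with models trained on four fifths and tested on one fifth. They are reduced to about 20 and turned into an individual score. No covariate is named in these steps.
5. Only then, "the predictive robustness of the individual score value will be challenged to identified confounding factors". These include BMI, age, pubertal state and gender, and the tool is a logistic regression.

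Muscular fitness is handgrip and standing broad jump (Section 2.3.2.7), and CRF is maximal oxygen consumption (Section 2.3.2.6). No age- or sex-specific reference is stated for either, although the article gives one for BMI and waist (Section 2.3.2.1). Section 2.6 also offers ANCOVA with BMI, age and gender, as an option in the general analyses.

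**The concern.** Strength, jump length and oxygen uptake may differ between an 8-10 and a 13-15 year-old who are equally active. In a pooled PCA, such a difference contributes to the leading axes, and the clustering then partly sorts by age group. If adolescents were also less active, fitness and PA would pull in opposite directions, and three clusters need not be ordered from low to high PA at all.

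Whatever separates the classes is what the selected markers will predict. A marker of age or puberty could enter the final set of about 20 as a PA marker, while a weaker true PA marker drops out. Hold-out testing gives no protection, because age predicts an age-driven class just as well in the held-out fifth. The study's main objective depends on these classes.

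The test in step 3 raises a separate problem. Clusters are formed to differ on their input variables, so a significance test on those same variables says nothing about whether the classes are real.

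**Working it through.** **Inputs from the documents.** 2 age groups x 3 BMI categories x 30 = 180, which agrees with the stated core cohort. The point disputes no figure in the plan.

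**Assumed inputs.** The documents give no age differences in fitness or PA, so a range was used, in within-age SD units. There were seven variables: handgrip, jump, oxygen uptake, light, moderate and vigorous PA, and a PA questionnaire score. One latent PA factor loads on them at 0.2, 0.4, 0.5, 0.5, 0.8, 0.8 and 0.5. Variables were z-scaled over the whole cohort, reduced to two principal components and cut into 3 Ward clusters, with 300 runs per row. Sex and BMI effects were not simulated.

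**Measures.**
- Cramér's V = sqrt(χ²/180) for the 3 x 2 table of class by age group. With two age groups, V² is the share of age-group variance explained by the classes.
- Majority-age share = sum over classes of the larger age-group count, divided by 180.
- PA share = variance of the latent PA factor explained by the classes.
- False marker = how often a marker shifted 1 SD by age group, and unrelated to PA, differs between classes at P < 0.05 without adjustment.

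| Shift: muscular / CRF / PA | V | Majority-age share | PA share | False marker |
|---|---|---|---|---|
| 0 / 0 / 0 | 0.10 | 0.54 | 0.57 | 6% |
| 0.5 / 0 / 0 | 0.15 | 0.56 | 0.57 | 7% |
| 1 / 0 / 0 | 0.29 | 0.63 | 0.55 | 39% |
| 1 / 0.3 / -0.5 | 0.44 | 0.69 | 0.50 | 65% |
| 2 / 0 / 0 | 0.60 | 0.76 | 0.49 | 85% |
| 2 / 0.3 / -0.5 | 0.69 | 0.81 | 0.45 | 97% |
| 2 / 0.5 / -0.8 | 0.80 | 0.88 | 0.38 | 99% |
| 3 / 0.5 / -0.8 | 0.91 | 0.95 | 0.32 | 100% |

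In variance terms, 2 / 0 / 0 gives 0.60² = 0.36 for age against 0.49 for PA. At 2 / 0.3 / -0.5 it is 0.69² = 0.48 against 0.45, and at 2 / 0.5 / -0.8 it is 0.80² = 0.64 against 0.38. So age overtakes PA only when CRF and PA also shift.

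A second simulation used four accelerometer and four fitness variables, with no age effect on accelerometry. At 1 SD on every fitness item, the classes explained 24% of the age-group variance and 47% of true PA. With shifts of 2-2.5 SD (handgrip), 1-1.5 SD (jump) and 1.5-2 SD (oxygen uptake), they explained 45-65% and 38-42%.

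**After correction.** With all seven variables standardised within age group, V is about 0.06, the majority-age share about 0.53 and the PA share about 0.56 in every row. The age-only marker is then significant in 2-6% of runs. If the pooled classes are kept and age is put into the marker test, that rate is 4-8%, but the PA share stays at its lower pooled value. The two corrections therefore do different jobs: adjustment stops age markers, and standardisation keeps the classes informative about PA.

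**Test of the clusters.** On data with no cluster structure (180 x 7), the classes were tested by the between-class share of the total sum of squares with 99 permutations, as a stand-in for PLS-DA. P = (1 + number of permuted values at or above the observed one)/100. On the variables that formed the clusters it rejected in 100% of 200 runs. On independent variables it rejected in 6.5%, where Monte Carlo error around 5% is sqrt(0.05 x 0.95/200) = 1.5 points.

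**The case against.** The strongest defence is that the article is silent on scaling rather than committed to unscaled values. Pre-processing before a PCA is often left to an analysis plan. That stands: a reader might infer that raw values will be used, and the text does not say so. But the article describes this pipeline down to the algorithm and the number of iterations, and the order it gives, selection first and confounders afterwards, is explicit.

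A reader might also infer that low and high PA will simply mean younger and older. The documents do not support this. Every age effect above is assumed, the link is weak at 0.5 SD, and PA still dominates at 1 SD. Nor is a claim about adiposity markers supported: no BMI effect was computed, and BMI category and sex are balanced across age groups by design ("Volunteers will be equally distributed between both sexes in each group and subgroup").

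The circularity is also an inference. The article does not name the predictors of the PLS-DA, and it selects no marker by this test. The order of steps makes circularity the natural reading, not a stated fact.

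Finally, phase 2 re-tests the score within persons over 6 months. Age group and sex are fixed within a person, so a score that mainly reflects them should not track change in PA. This limits false claims, but phase 2 measures only candidates already selected. Its 6-month visit in Table 1 also lists no CRF or muscular fitness test, so the baseline classification cannot be repeated in the same form. The ANCOVA of Section 2.6 is optional and is not attached to class definition or selection.

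**Conclusion.** The point holds in conditional form. As written, one clustering over both age groups defines the PA classes, no age or sex scaling is stated, and confounders are examined after selection. If fitness differs between the age groups by about 1 SD or more, the classes partly reflect age group (majority-age share 0.63-0.69). At about 2 SD or more they mostly do, in the sense that class alone places 76% or more of participants in the right age group. Markers of age or puberty may then be selected as PA markers, and PA markers already discarded cannot be recovered by the later check. These sizes rest on assumed shifts and loadings; at 0.5 SD or less the problem is small.

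On the natural reading, the permutation test of the clusters is not evidence that the classes are real. This is more than a missing detail, because the stated order of steps affects which markers are found.

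**What to change.** 1. Standardise the muscular fitness and CRF variables within age group x sex before the PCA, or cluster within age group. Check that the clusters are ordered on accelerometer PA. Leave accelerometer PA unstandardised in the reporting and show it by age group and sex, so that real PA differences stay visible.
2. Include age group and sex in marker selection inside each training fold. Report the gain of the score over a base model with age group, sex and BMI z-score. Show selection with BMI z-score adjustment as a sensitivity analysis only, because BMI may lie on the pathway from PA to health. Do not adjust for recruitment source: sports academies and a cardiovascular risk unit (Section 2.3.1) may stand in for PA itself.
3. Replace the PLS-DA significance test on the clustering variables by a cluster-stability measure such as the bootstrap. If the clusters are unstable or not ordered on PA, use the continuous PA axis.

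The cost is analysis work only, since the variables needed are already collected. The downside is fewer and weaker-looking markers, and standardisation removes fitness differences between age and sex strata. The simulated correction standardised all seven variables, while step 1 standardises fitness only. Where PA itself differs by age group, some link between class and age will therefore remain, and step 2 is needed to handle it.

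### Agreement of PLS-DA, sparse PLS and random forest on a variable is not independent confirmation and carries no false-selection rate; depending on the cut-offs, pure noise can supply a number of the same order as the expected 20.

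*Protocol article*

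**What the plan says.** Section 2.6.1 (Integrated analysis) first forms the PA classes by clustering the PA and fitness measures, "in order to extract 3 clusters corresponding to low, medium, and high PA scores". Differences between these clusters are tested by a supervised model with a permutation test. Markers are then chosen block by block: "Variables selection to fit the class assignment will be performed independently for each kind of variable with a sight of sparsity". The tools are PLS-DA (orthogonalised or not), sparse PLS and machine learning, and the retention rule is "machine-learning methods such as random forest will be applied and resilient variables, selected with all the methods, retained".

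The same section adds resampling: "Statistical models will be built on 4/5 of the population, and their performance assessed by predicting the 1/5 unknowns", and "This will be iterated 10 times". It also says "Complementary AUROC analyses will confirm biomarkers selection robustness". The final yield is given as "expected ∼20 variables from any origin". These variables enter a last PLS-DA, which gives the scoring equation.

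The article names FDR correction only in section 2.6, for differential gene expression. Section 2.5 sends candidates from phase 1 to assay in phase 2.

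**The concern.** The rule treats agreement between methods as evidence that a variable is real. That would be reasonable if the methods were separate replications. They are not: each scores a variable by how well it separates the same labels in the same children, and PLS-DA, its orthogonalised form and sparse PLS are close variants of one method. A variable that separates the classes by chance in this sample will usually rank high in all of them. Agreement therefore says that the methods are alike, and much less about whether the association would hold in other children.

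The retained variables become the candidate biomarkers, are assayed in phase 2 and make up the score. Without an error rate at this step, the sponsor cannot say how many of the retained markers to expect by chance.

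**Working it through.** **The plan's own figure.** The expected 20 or so is stated without a formula or cut-off, so it cannot be reproduced. The check asks what the consensus rule yields when there is no signal.

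**Inputs from the article.** Three classes (2.6.1); ten 4/5 to 1/5 splits (2.6.1); about 2,000 miRNAs in 6 × 15 = 90 children (2.5); RNA-Seq in 90 children (2.5); metabolomics in the core cohort of 180 (2.5, 2.3.1).

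**Assumptions.** Equal class sizes; independent standard-normal noise; PLS-DA with 2 components ranked by VIP; sparse PLS with 2 components keeping k variables on each; random forest with 300 trees ranked by importance. The cut-off k is not in the article, so it is varied.

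**Step 1: one block, one pass, p = 2,000.** If the methods were independent, the expected agreement would be p × (k/p)³ = k³/p². For k = 50 that is 125,000 / 4,000,000 = 0.031. Mean number of noise variables selected by all three methods (8 data sets per cell):

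| k | k³/p² | n = 90 | n = 180 |
|---|---|---|---|
| 10 | 0.00025 | 3.1 | 2.5 |
| 20 | 0.002 | 6.8 | 5.1 |
| 50 | 0.031 | 18.5 | 16.6 |
| 100 | 0.25 | 37.9 | 36.9 |

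Six further data sets per sample size at k = 50 gave 16.8 (n = 90) and 14.0 (n = 180). A separate set of runs gave 1 to 6 at top 10 to 20, 15 to 19 at top 50 and 33 to 34 at top 100. Together: roughly 1 to 7, 14 to 19, and 33 to 38. Runs that included 1,500 variables in correlated blocks gave 15 to 16 at top 50 and 32 to 36 at top 100, so independence of the noise does not drive the result. A looser rule (VIP above 1, sparse PLS 100 per component, forest top 200) gave about 80.

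**Step 2: sum over blocks.** The plan's 20 is a total over all data types, so this is the like-for-like comparison. Block sizes of 5,000 genes, 1,000 metabolites and 40 clinical variables are assumed, beside the 2,000 miRNAs. Mean totals over 3 data sets:

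- all four blocks: k = 5, 6.3; k = 10, 11.0; k = 15, 24.7;
- the three large blocks only, because 40 variables are too few for these cut-offs: k = 20, 19.7; k = 25, 22.3; k = 50, 46.0.

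Looser cut-offs gave 16 to 97. The expected 20 lies inside these ranges.

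**Step 3: all three methods rerun in each 4/5 training set (p = 2,000, k = 50, 6 data sets).** About 17 noise variables pass per split.

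| Recurrence | k = 50 | looser cut-off |
|---|---|---|
| at least 5 of 10 | 5.5 to 5.7 | 13.0 to 13.2 |
| at least 8 of 10 | 1.0 to 1.5 | 2.5 to 2.8 |
| 10 of 10 | 0 | 0.3 to 0.7 |

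Mean held-out AUROC was 0.52 (n = 90) and 0.48 (n = 180).

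**Step 4: variables selected once on everyone, only the final model split.** The same noise gave held-out AUROC of 0.89 (n = 90) and 0.78 (n = 180).

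**The case against.** - **The counts rest on cut-offs that are not the plan's.** True. A strict cut-off gives a handful in one block and a loose one gives dozens. A reader might infer that noise supplies about 20 as a fixed result; the article does not support that, because it states neither cut-offs nor most block sizes.
- **The 20 is a forecast, not a quota.** Also true. Nothing in section 2.6.1 forbids a shorter list or an empty one, so it does not follow that a null study would necessarily report 20 markers. It could.
- **The splits and AUROC would expose noise.** They would if selection is repeated inside each training set (Step 3), and recurrence in at least 8 of 10 splits would cut the noise to about 1 to 3 per block. The article does not say that selection is nested and sets no recurrence threshold. If selection is done once on all children, the AUROC check would endorse noise (Step 4). An inference that the checks certainly fail is not supported either.
- **There are later filters.** Section 2.5 takes leading transcripts and miRNAs from 90 sequenced children to RT-qPCR in all 180, half of whom were not sequenced. This helps for those two data types, although the 180 include the discovery children, and metabolomics has no such unsequenced half. The phase 2 challenge uses a subgroup of the same cohort.
- **Cut-offs and nesting belong in the full protocol or SAP.** Agreed, and their absence is not the point. The point is a criterion the article does fix: agreement between methods is the ground for retention, and agreement has no known error rate until it is calibrated.

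**Conclusion.** The concern holds in limited form. Consensus among PLS-DA, sparse PLS and random forest on the same children and labels does not control false selection. At top 50 in a block of 2,000, noise passes at 14 to 19 variables, against 0.03 if the methods were independent. Requiring all methods does shorten the list compared with any one of them, but by far less than independent confirmation would.

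The FDR correction in section 2.6 is tied to differential expression, and the permutation test in section 2.6.1 to the PA clusters before markers are chosen. Neither attaches an error rate to the selection. Whether noise alone would approach the expected 20 depends on the cut-offs and the recurrence rule: the totals over blocks ran from about 6 to 97 in one pass, and recurrence in at least 8 of 10 splits leaves about 1 to 3 per block.

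The size rests on equal classes, assumed block sizes and 3 to 8 data sets per setting, so the counts are approximate. The direction does not depend on these choices.

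**What to change.** Keep the multi-method consensus if wished; replacing it by a single selector is a matter of preference. Change the text of section 2.6.1 so that:

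1. the whole selection, all methods included, is rerun inside each 4/5 training set, and each variable's selection frequency is recorded;
2. the same pipeline is repeated on at least 200 permutations of the PA labels;
3. a variable is retained only if its frequency exceeds the 95th percentile of the maximum frequency under permutation, or under an equivalent stated bound on expected false selections per block;
4. the number of variables expected under the null is reported beside the number retained, which may be below 20 or zero.

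One practical point: ten splits give frequencies only in tenths, and with looser cut-offs some noise variables were already selected in 10 of 10. The permuted maximum could then sit at the ceiling, where nothing can exceed it. Many more resamples, preferably half-samples, avoid this.

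The cost is wording and computing time, and probably a shorter panel. No added samples, visits or assays are needed.

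### Each child's 95% confidence interval, if taken from the final PLS-DA as the stated order implies, ignores variable selection and does not show how surely that child is placed in a PA class

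*Protocol article*

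**What the plan says.** All of this is in the protocol article, section 2.6.1 (Integrated analysis), except the cohort size. The steps run in this order:

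1. Three PA classes are obtained by clustering principal-component scores of the PA and fitness measures.
2. Biological variables are chosen against those classes: "Variables selection to fit the class assignment will be performed independently for each kind of variable with a sight of sparsity".
3. Several methods are run and only the variables common to all are kept: "PLS-discriminant analysis (orthogonalized or not), sparse-PLS, and machine-learning methods such as random forest will be applied and resilient variables, selected with all the methods, retained".
4. Performance is checked by repeated splitting, ten times: "Statistical models will be built on 4/5 of the population, and their performance assessed by predicting the 1/5 unknowns". AUROC analyses are added to confirm that the selection is robust.
5. The survivors are refitted: "The most resilient variables (expected ∼20 variables from any origin) will be saved, and computed in a final PLS-discriminant analysis".
6. The coefficients of that last model give an equation whose purpose is "to give each individual a score value (with 95% confidence intervals) that fits its PA class".
7. Finally, "This equation will be challenged in the subgroup of the core cohort after the educational intervention".

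Section 2.3.1 sets the cohort: "A total of 180 volunteers (core cohort) will be recruited". Section 2.5 gives about 2,000 candidate miRNAs, with RNA-Seq and untargeted metabolomics in addition. RNA-Seq covers 90 children, and miRNA sequencing covers 15 in each of 6 groups, also 90. No separate sample is named for the final fit.

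**The concern.** There are two separate problems with the interval.

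**Selection.** The same children supply the class labels, the choice of variables and the final coefficients. Variables that survive a search of thousands of candidates look more strongly related to class than they are. An interval computed from the final model starts after that search. It reflects sampling error in about 20 coefficients, but neither the upward bias nor the chance that another sample would have produced a different 20.

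**Type of interval.** The score is meant to match one child to a class. A confidence interval says how precisely the equation is known at that child's values. It does not include how far children scatter around the equation, and that scatter decides whether a child can be placed in one class and not its neighbour.

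The score is the study's main product, and the Discussion hopes that the biomarkers will help identify non-responders and support personalised advice. Error bars that are too narrow would make the score look more decisive for individuals than it is.

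**Working it through.** **The plan's own figure.** The stated level is 95%. It cannot be reproduced, because the article gives no variance formula, resampling scheme or target. What can be checked is how an interval from the final model would behave.

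**Confidence versus prediction width.** Take a least-squares analogue with 20 terms plus an intercept and n = 180. The average squared standard error of a fitted value is 21/180 of the residual variance.

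- Confidence half-width: 1.96 × √(21/180) = 0.67 residual SD.
- Prediction half-width: 1.96 × √(1 + 21/180) = 2.07 residual SD.
- Ratio: 2.07 / 0.67 ≈ 3.1.

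This shows the order of the difference. It is not an exact PLS result.

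**Coverage by simulation.** From the documents: n = 180 or 90, about 20 variables kept, three classes, NIPALS PLS. Assumed: equal classes coded -1/0/1, independent normal predictors, the top 20 by marginal correlation with class, two PLS components, 500 or 2,000 candidates, and interval = score ± 1.96 × bootstrap SE. The signal ranged from none to 20 true markers with a latent R² of 0.6. Expected score means the expected class code given the true markers.

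| Interval, nominal 95% | Expected score, cohort | Expected score, new children | Actual class code, cohort | Actual class code, new children |
|---|---|---|---|---|
| 20 selected variables held fixed | 37-63% | 40-64% | 44-62% | 25-33% |
| 20 variables named beforehand (n = 180) | 91-95% | 89-95% | 38-49% | 36-45% |
| Selection repeated in the bootstrap (n = 180, 2,000 candidates; only 10 data sets per setting) | 86-88% | 78-91% | 86-88% | 52-58% |

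A second, separately built simulation (n = 180, 3,000 candidates, new children) gave 33-54% for the expected score after selection, against 80-90% with variables named beforehand. For the actual class code it gave 23-26% and 35-47%.

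**What the rows separate.**

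- *Selection.* At n = 180, 2,000 candidates and the same three signal settings as the third row, coverage of the expected score in the cohort is 44-50% with selected variables held fixed and 86-88% with selection repeated. Ignored selection therefore causes most of that loss.
- *Interval type.* With no selection at all, the confidence interval still contains the actual class code in only 36-49% of children (35-47% in the second simulation). That is how a confidence interval behaves, and it is the wrong tool for placing a child.
- *Changing the label is not enough.* Adding the final model's residual variance to the fixed-variable interval covers a new child's class code in 69-88% of cases after selection. Adding it to the bootstrap with selection repeated gives 87-92%. The in-sample residuals are too small: at n = 180 and 2,000 candidates the final model's R² is 0.52-0.57 in the cohort and 0.002-0.09 in new children.

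**Whether another step repairs it.** The 4/5-1/5 splits measure classification performance, and AUROC addresses the selection. Neither calibrates an interval for one child. The challenge after the intervention re-measures a subgroup of the same cohort and brings in no fresh children.

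**The case against.** The strongest reply is that the article never says the interval ignores selection. Resampling the whole pipeline would not contradict its wording, and a condensed article may leave the construction to the full plan. This stands as a limit on the claim. A reader might infer that the plan states an invalid interval, but the text does not go that far. What remains is that the article fixes a sequence in which the interval comes out of the refitted model, names it a confidence interval, and describes no step that carries selection into it.

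A reader might also conclude that the interval contains the child's true position only about a quarter of the time. The documents do not support that. They define no such target and no -1/0/1 coding, and a confidence interval is not designed to contain a class code. The lowest figures also concern new children, whereas the article scores children of the cohort, who already have a class from measured PA and fitness. Coverage of the class code in the cohort is 44-62%.

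The size depends on assumptions. The article selects within each kind of variable, keeps only variables that every method picks, and narrows miRNAs to at most 20 before whole-cohort RT-qPCR; the simulations simplify this. The target matters too. In a rerun of the second simulation's settings, coverage in new children was 49-56% for the expected class given all true markers, and 56-66% given only the variables in the equation. The direction did not change in any setting.

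Finally, no passage uses these intervals to judge a child's change from before to after the intervention, and personalised advice is an expectation in the Discussion. Harm of that kind is a possible later use and not something the plan prescribes.

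**Conclusion.** The point holds conditionally on selection and directly on interval type. If the interval is computed from the final PLS-DA, as the stated order implies, it will cover a child's expected score well below 95%, at roughly 35-65% in the settings tried. That range rests on the assumed coding, candidate numbers, selection rule and signal, and it illustrates the size without predicting this study's figure. Whatever is done about selection, a confidence interval does not say how surely one child falls in a PA class. The severity is moderate. The construction is implied and not stated, the study is an exploratory first validation step, and the remedy needs no new participants or assays.

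**What to change.** In section 2.6.1, replace the phrase on 95% confidence intervals with wording such as: *Each individual's score is reported with a 95% prediction interval, or with the set of PA classes not excluded at 95%, based on out-of-fold predictions, with variable selection and model fitting repeated inside each resample.* If an interval for the equation itself is also wanted, label it as such and bootstrap selection and fit together.

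The exact resampling method can be left to the analysts; jackknife+ and cross-conformal intervals are two options among several.

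One practical limit should be stated. Metabolomics and lipidomics are measured in all 180 children, so selection can be repeated across the whole cohort. For RNA-Seq and miRNA sequencing it can be repeated only within the sequenced subsets of 90, because the other children receive RT-qPCR only for markers already chosen.

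The cost is more computing and wider reported intervals, about threefold in the least-squares analogue. Some children's intervals will then include more than one class, which is an honest description of what the score can tell about them.
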